### 1.2. Primary and Secondary Objectives

The objectives of this study will be measured in two compared groups.

Primary objective: To assess the impact of telenursing interventions on the supportive care needs (SCNs) [18,19] in patients with lung cancer and melanoma at the first prescription of TT after one month of treatment (T1). Secondary Objectives: To explore the differences between the AEs reported by healthcare professionals and the patient-reported outcomes and develop a specific nursing reporting system to improve the quality, safety and continuity of cancer care. Further secondary outcomes are shown in Table 1, together with the tools, timing, and users involved in the data collection. Among the secondary outcomes, the SCNs over time (until the end of the study) [18,19], quality of life [20,21], patient satisfaction [22,23], therapeutic adherence [24,25] and performance status [26] will be assessed and compared in both groups. Moreover, the incidence and severity of the following vital signs and adverse events will be compared to highlight the effectiveness of the telenursing intervention with tools based on the Common Terminology Criteria for Adverse Events (CTCAE) [27]: body temperature, blood pressure, heart rate, body weight, pain, stomatitis and mucositis, dysgeusia, nausea and vomiting, diarrhoea, loss of appetite, fatigue, headache, dermatologic reactions, cough and dyspnoea, pain, palmar–plantar erythrodysesthesia, bleeding events, photosensitivity, ophthalmological reactions, sleep, mood and voice disorders.

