They will provide the following:Nursing assessment: to allow comparison between the two groups, the questionnaires described in Table 1 will be used at baseline and according to the timing described in Table 1. The measurements will allow researchers to highlight the effectiveness of the telenursing intervention and the improvement of patients’ clinical path.Support in study procedures: during the 6-month follow-up, nurses will provide advice to the patients involved to improve the experience with the intervention and the tools used, and also in order to optimize the data collection in the two compared groups.Intervention in the IA: with patients involved in the experimental group, research nurses will use telenursing to monitor the supportive care needs and other objectives described in Section 1.2. For the purposes of the study, the telenursing intervention will use the Intelligence2health platform for video calls, a dedicated telephone line, short messages and electronic tools. During the 6-month study, nurses will implement a total of 8 video calls. Nurses will implement patient education interventions to improve patient care, quality of life, satisfaction, treatment adherence, problem-solving skills, and self-care. Suggestions to better manage patients’ needs will be evidence-based and may be agreed with medical oncologists as needed. However, they will be kept constantly updated on the health status of patients. Nursing interventions will be aimed at promoting the care needs of patients.Data collection will be carried out using the chosen tools, according to the timing described in Table 1, at baseline, daily, after 30, 90 and 180 days, to allow comparison between the intervention arm and control arm. In particular, patients and nurses will monitor the burden and needs related to care through the Supportive Care Needs scale [18,19]; therapeutic adherence through the MARS-5I [24,25]; QoL through the QoL SF-36 [20,21]; satisfaction and usability of the system through the SUS [22,23]; performance status through the Karnofsky performance status [26]; and the AEs described in Section 1.2 through the CTCAE tools [27]. Patients enrolled in the control group will use paper questionnaires, while patients in the intervention group will use electronic tools that nurses will check daily to implement any coaching interventions. Any changes in the health status or needs of patients can be intercepted early thanks to the filling out of daily forms by the patients themselves, which nurses will check daily.Creation and management of a specific database.

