#### 2.4.1. Control Arm

The CA patients will attend monthly visits with oncologists and receive in-person nursing care as needed. They will fill out paper-form questionnaires collected by nurses during the monthly visits until the end of the study. Nurses and oncologists will not consider patient data during follow-up, and according to clinical practice, patients should contact oncologists as needed. Data collected by nurses during the monthly visits and by patients at home will be recorded in a specific database by the nurses, but these data will not be evaluated by nurses or oncologists during the study. However, according to current clinical practice, if necessary, patients in the control group will be able to contact oncologists and nurses via the telephone and email addresses provided before the start of the study.

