## Figures and Tables

**Table 1 mps-07-00078-t001:** Outcomes and tools.

Time	User	Outcomes	Tools (Citation)
Monthly	Nurse/Clinician	Adverse events	Common Terminology Criteria for Adverse Events
T0	Nurse	Clinical-anamnestic-demographic data	Registry card
Daily	Patients	Vital signs and main symptoms from patient-reported outcomes	Patient-reported outcomes
T0, T1, T2, T3	Patients	Patient-reported outcomes	Patient-reported outcomes
T0, T1, T2, T3	Nurse/Clinician	Performance status	Karnofsky performance status
T0, T1, T2, T3	Patients	Quality of life	Quality of Life SF-36
T1, T2, T3	Patients	System satisfaction and usability	SUS—System Usability Scale
T0, T1, T2, T3	Patients	Supportive care needs	Supportive care needs
T0, T1, T2, T3	Patients	Therapeutic adherence	MARS-5I

T0: baseline; T1: 30 days; T2: 90 days; T3: 180 days; SF: short form; MARS-5I: Medication Adherence Report Scale Italian.

**Table 2 mps-07-00078-t002:** Participants’ timeline.

Timeline (People Involved)	T0 Baseline	T1 Month 1	Month 2	T2 Month 3	Month 4	Month 5	T3 Month 6

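### Satisfaction is to be compared between arms with the System Usability Scale, but the system it rates is given to one arm only, so the difference is not an effect of telenursing on satisfaction

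*Protocol article*

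**What the plan says.** Section 1.2 opens its objectives with a general rule: "The objectives of this study will be measured in two compared groups". Among the secondary outcomes it then states that "patient satisfaction [22,23], therapeutic adherence [24,25] and performance status [26] will be assessed and compared in both groups".

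Section 2.4 names the instrument under the same two citations: "satisfaction and usability of the system through the SUS [22,23". It gives the purpose of the data collection that includes this instrument as "to allow comparison between the intervention arm and control arm", and says of the Table 1 tools that, "to allow comparison between the two groups, the questionnaires described in Table 1 will be used at baseline and according to the timing described in" that table. Table 1 lists the outcome as "System satisfaction and usability", measured by the SUS at T1, T2 and T3 and completed by patients. It carries no note restricting it to one arm. No other satisfaction instrument appears in the article.

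On what each arm uses, section 2.4 says: "Patients enrolled in the control group will use paper questionnaires, while patients in the intervention group will use electronic tools". Section 2.4.1 says of the control arm: "They will fill out paper-form questionnaires collected by nurses during the monthly visits". It adds monthly oncology visits, in-person nursing as needed, and contact by telephone and email. Section 2.4.2 gives intervention patients, on top of usual practice, a link to the electronic questionnaires, a link to the Intelligence2health video platform and a company telephone number.

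**The concern.** A usability scale scores the thing the respondent has been using. For an intervention patient that is reasonably clear: the platform and the electronic forms. For a control patient the article defines nothing equivalent. The respondent could score the paper forms, the clinic visits or the telephone and email route, could answer in general terms, or could leave the form blank.

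Satisfaction is one of the outcomes on which the trial intends to compare its arms. If the plan is followed as written, the analysis will yield a between-arm SUS difference and possibly a p-value at each of three visits. Neither would have a clear interpretation. A high platform score against a low score for paper forms could be taken for greater satisfaction with care. A null result could equally be taken as evidence that telenursing does not affect satisfaction. Neither conclusion would follow.

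**Working it through.** The plan gives no figure for the SUS comparison: no assumed mean, SD or difference. The check is therefore a reading of the provisions side by side.

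1. **Is a between-arm comparison of satisfaction planned?** Yes. Section 1.2 says so expressly, and section 2.4 repeats the purpose for the set of tools that includes the SUS.

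2. **Is the SUS the instrument for that comparison?** Yes. Section 1.2 attaches citations 22 and 23 to patient satisfaction, and section 2.4 attaches the same citations to the SUS. Table 1 joins satisfaction and usability in one row with the SUS as the only tool.

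3. **Is the SUS limited to one arm?** No. Table 1 gives the user as patients, as it does for quality of life, supportive care needs and adherence, which are all collected in both arms. The only sign that the SUS is treated differently is that it is not scheduled at T0. That fits a scale needing prior use of something, but it does not say which patients complete it.

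4. **What is there to rate in each arm?**

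| | Intervention arm | Control arm |
|---|---|---|
| Video platform | yes (2.4.2) | not provided |
| Study questionnaires after baseline | electronic (2.4, 2.4.2) | paper (2.4, 2.4.1) |
| Visits under usual practice | yes | yes |
| Telephone contact | company number for the study nurses (2.4.2) | ordinary telephone and email (2.4.1) |
| Object of the SUS | platform and e-tools, by the natural reading | not defined |

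5. **What does the contrast estimate?** Write the mean SUS score as S(arm, object). The plan would compute

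 S(intervention, platform and e-tools) − S(control, whatever the patient has in mind).

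 Arm and object change together. An effect of arm on satisfaction needs the object held fixed. It cannot be fixed at the platform, because control patients do not have it. It could be fixed at care received, but nothing in the article directs the SUS to that. Randomisation balances the patients. It does not make the two ratings measurements of the same thing, and neither a larger sample nor better handling of missing data would change that.

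6. **Does this reach the primary analysis?** No. Section 2.2 sizes the trial on supportive care needs at one month, and that calculation reproduces. The difference is 103.5 − 81.53 = 21.97. The pooled SD is √((13.2² + 21.96²)/2) = 18.12. The effect size is 21.97/18.12 = 1.21. The t-based solution is 15.32, rounded up to 16 per arm or 32 in total, and 32/(1 − 0.20) = 40. None of this involves the SUS.

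**The case against.** The best defence is that this is loose drafting in a condensed article. The authors leave the SUS out at baseline, so they evidently know it needs prior exposure. Section 2.4 and Table 1 speak of the system, not of care. The full protocol or the control-arm form may say who completes the scale and about what. That makes an intended restriction to the intervention arm plausible, but it does not cure section 1.2, which affirmatively says satisfaction is compared in both groups. If the restriction was intended, that sentence is wrong and needs the same edit.

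A second defence is that control patients do have something to rate: forms, visits, telephone and email. This is fair, and it rules out the claim that they would be rating nothing. What remains is that the article does not say which of these they rate, and that none of them is the platform.

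A third is that the article names no specific SUS test, since section 2.7 gives only general methods. This also stands. The comparison is stated, but the number and form of the tests are inferred. Nor does the article say that a difference would be presented as a satisfaction benefit. That is a risk of the design and not a stated intention.

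A reader might also infer that control patients who leave the SUS blank could be removed under section 2.5. The article does not support that. The rule there allows exclusion after 15 days of missing data, which fits the daily forms. It does not clearly reach a single questionnaire due at three visits when the patient's other forms are complete.

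**Conclusion.** The point holds as a defect in one secondary outcome. As written, the plan compares SUS scores between arms that would be rating different objects, with the control arm's object undefined. The difference cannot be interpreted as an effect of telenursing on satisfaction at T1, T2 or T3. This rests on two assumptions: that the SUS is the only satisfaction instrument, which is all the article shows, and that no unseen control-arm form redirects the scale to something common to both arms.

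The size is best stated as one secondary comparison at three time points. It is tempting to count control forms: 20 × 3 = 60 with full retention, or 16 × 3 = 48 after the planned 20% drop-out. Those figures count paperwork and do not measure bias, so they should not be offered as the magnitude. The SUS remains a sensible measure within the intervention arm, and the primary outcome and sample size are unaffected. The change is worth making because it is cheap and removes a comparison that cannot be interpreted.

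**What to change.** In sections 1.2 and 2.4 and in Table 1, state that the SUS is completed by intervention-arm patients only and refers to the telenursing platform and electronic tools. Report it descriptively at T1, T2 and T3 as mean, SD and 95% confidence interval. In section 1.2, remove satisfaction measured by the SUS from the outcomes compared in both groups.

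Optionally, if the investigators want a between-arm statement about satisfaction, they need a measure of satisfaction with care that applies equally to both arms and is worded identically in each. That would be a new outcome whose choice and validity they would have to justify. The correction does not depend on it.

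The cost is one planned secondary comparison, which was not interpretable, and a minor amendment to go to the ethics committee, as section 2.8 requires for protocol changes. If the trial registration lists the comparison, that entry would need the same edit. Control patients have one questionnaire fewer to complete at each of three visits.

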## 2. Materials and Methods

The Standard Protocol Items Recommendations for Interventional Trials (SPIRIT) checklist [28] was used to report this study protocol (Supplementary Table S1).

Supplementary Table S1. Standard Protocol Items Recommendations for Interventional Trials (SPIRIT) checklist.

### 2.1. Experimental Design

A six-month, double-arm, prospective, monocentric, RCT will be performed to assess the impact of a telenursing intervention on the reduction of the treatment-related burden in patients with lung cancer and melanoma on TT, improving their clinical pathway. The telenursing intervention will be added to clinical practice (intervention arm, IA) to highlight differences in the study’s outcomes compared to the control group (control arm, CA), which was followed according to clinical practice.

### 2.2. Study Setting and Sampling

The RCT will be performed in a national cancer centre starting on 1 April 2024. A nursing team will lead the project in collaboration with medical oncologists. The sample size calculation was performed on the primary outcome, the SCNs scale [18,19] measured one month after treatment, considering possible losses to follow-up (drop-out rate). The study by Ebrahimabadi [18] allowed the researchers to hypothesise the following:A mean score and its relative standard deviation (SD) in the intervention group equal to 81.53 (±13.2),A mean score and its relative SD in the control group equal to 103.5 (±21.96), with a statistical power of 90% and a significance level α = 0.05, while a two-tailed Student’s *t*-test estimated an overall size of 32 patients, 16 for each group. Given the mean score reported in the hypothesis system, we obtain an effect size equal to 1.21. Considering a drop-out rate of 20%, we will enrol a total sample of 40 patients. The software NCSS PASS v.11.0 was used to assess the minimum size. Evaluation of the statistical tests will be carried out by an expert statistician.

### 2.3. Inclusion and Exclusion Criteria

Inclusion criteria: oncological outpatients with melanoma and lung cancer, 18–75 years old, on the first prescription of TT; able to understand and speak the national language; patients with internet access and a personal computer, or smartphone or tablet device; and able to sign an informed consent and willing to adhere to the procedures of the study. Exclusion criteria: patients affected by other malignancies, previously treated with TT; patients with concomitant cancer treatment (chemotherapy, radiation therapy, immunotherapy, and exclusive palliative care) and patients with poor compliance interfering with study procedures. The exclusive inclusion of patients naïve to TT aims to reduce the potential bias related to the effect of previous educational interventions to prevent and monitor care-related needs. Nurses and oncologists will introduce the study to all eligible patients of the oncological department during the follow-up visits. Eligible patients will be given a copy of the informed consent, setting a subsequent appointment within 7 days for the enrolment visit (baseline) and agreeing to formal adherence to the study by signing the aforementioned informed consent.

### 2.4. Detailed Procedure

Two research nurses (PhD and PhD student) with previous experience in telenursing and cancer treatment with TT [11,29] will be involved from the patient enrolments to the end of the study. The research nurses involved will introduce the project to interested patients, explaining the objectives, purposes, and procedures of the study and the implications for clinical practice.

They will provide the following:Nursing assessment: to allow comparison between the two groups, the questionnaires described in Table 1 will be used at baseline and according to the timing described in Table 1. The measurements will allow researchers to highlight the effectiveness of the telenursing intervention and the improvement of patients’ clinical path.Support in study procedures: during the 6-month follow-up, nurses will provide advice to the patients involved to improve the experience with the intervention and the tools used, and also in order to optimize the data collection in the two compared groups.Intervention in the IA: with patients involved in the experimental group, research nurses will use telenursing to monitor the supportive care needs and other objectives described in Section 1.2. For the purposes of the study, the telenursing intervention will use the Intelligence2health platform for video calls, a dedicated telephone line, short messages and electronic tools. During the 6-month study, nurses will implement a total of 8 video calls. Nurses will implement patient education interventions to improve patient care, quality of life, satisfaction, treatment adherence, problem-solving skills, and self-care. Suggestions to better manage patients’ needs will be evidence-based and may be agreed with medical oncologists as needed. However, they will be kept constantly updated on the health status of patients. Nursing interventions will be aimed at promoting the care needs of patients.Data collection will be carried out using the chosen tools, according to the timing described in Table 1, at baseline, daily, after 30, 90 and 180 days, to allow comparison between the intervention arm and control arm. In particular, patients and nurses will monitor the burden and needs related to care through the Supportive Care Needs scale [18,19]; therapeutic adherence through the MARS-5I [24,25]; QoL through the QoL SF-36 [20,21]; satisfaction and usability of the system through the SUS [22,23]; performance status through the Karnofsky performance status [26]; and the AEs described in Section 1.2 through the CTCAE tools [27]. Patients enrolled in the control group will use paper questionnaires, while patients in the intervention group will use electronic tools that nurses will check daily to implement any coaching interventions. Any changes in the health status or needs of patients can be intercepted early thanks to the filling out of daily forms by the patients themselves, which nurses will check daily.Creation and management of a specific database.

After nurses have obtained the informed consent, 40 patients with melanoma and lung cancer (20 in each group) will be randomised into the IA (telenursing intervention added to clinical practice) or the CA (clinical practice). To allow for comparison, at baseline (T0) before the randomisation, patients from both groups will complete the tools shown in Table 1 in paper format. Additionally, patients involved in the study will use the study tools according to the timelines described in Table 1 at T1 (30 days), T2 (90 days), and T3 (180 days). Regarding the practice procedures, monthly telenursing interventions will be provided every 30 days, on dates agreed in advance with patients. However, patients will be able to communicate with the nursing staff via short messages or by telephone at any time of the day, between 8 a.m. and 2 p.m. An unplanned nursing intervention can be useful in case of patient doubts or problems related to therapeutic adherence (dosage errors, forgotten or double doses, etc.), onset of new side effects, sudden alterations in vital signs, etc. In addition, in view of the daily questionnaire filled out by patients (Table 1), nursing staff will implement additional interventions as needed, remotely or in person.

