#### 2.4.2. Intervention Arm

In addition to clinical practice, after the randomisation, the IA patients will receive an educational nurse intervention to improve the SCNs [18,19], prevent the main AEs and recap the study procedures. Furthermore, at baseline, the IA patients will receive the following:A link to access the electronic questionnaires through a web platform (GDPR and privacy compliant) (daily, at one, three and six months).A link to access the platform Intelligence2health [30], actually used in the same national cancer centre for the monthly telenursing interventions.A company telephone number to contact the team nurses.

In the first month, nurses involved in the study will carry out two telenursing interventions through a video call enabled by the platform (Table 2). The first virtual meeting will be conducted seven days after baseline (T0), focusing on the study procedures and e-tools. Subsequent telenursing interventions will be carried out monthly. Research nurses will review the daily data from the IA patients to arrange appropriate reinforcement interventions (coaching), agreed upon with oncologists where applicable. However, the oncologists will be steadily updated on the patients’ clinical conditions. The telenursing interventions will aim to prevent, monitor and improve treatment-related outcomes (Table 1). Specifically, evidence-based nursing coaching interventions will aim to improve the SCNs [18,19], adverse events and vital signs described in the primary and secondary objectives, and what will be required by patients regarding treatment-related needs.

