### 2.6. Data Collection

The planning of the study will include an enrolment period lasting 12 months, starting from the involvement of the first patient after 15 June 2024. The study follow-up will last six months. After this period, all the patients will be referred to current clinical practice. Nurses will record digital data from patients’ self-reports and nurses’ interviews and observations in a specific database.

Patients in the control arm will be treated according to current clinical practice, mainly with the support of oncologists. The paper questionnaires that patients and nurses will complete during the study will be recorded by nurses in a specific database.

Data from patients enrolled in the intervention group will be collected via electronic questionnaires, similar to those of nurses. Data collection for the outcomes described in Table 1 will be assessed at baseline (T0), after 30 (T1), 90 (T2) and 180 days (T3). In addition, patients will transmit data daily relating to the monitoring of vital parameters and AEs described in the section on the primary and secondary objectives.

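### The daily symptom and vital-sign record is captured differently in the two arms, so it should not be used for between-arm comparison

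*Protocol article*

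**What the plan says.** - **Daily record.** Table 1 has a daily, patient-completed row, "Vital signs and main symptoms from patient-reported outcomes", not limited to either arm. Section 2.4 (Detailed Procedure) names daily collection, alongside baseline and days 30, 90 and 180, as serving comparison of the two arms.
- **Use.** Section 1.2 states that "the incidence and severity of the following vital signs and adverse events will be compared to highlight the effectiveness of the telenursing intervention", and the sentence goes on to name CTCAE-based tools. Section 2.6 says that "patients will transmit data daily relating to the monitoring of vital parameters and AEs", and refers back to the Section 1.2 list for those items.
- **Mode by arm.** Section 2.4: "Patients enrolled in the control group will use paper questionnaires, while patients in the intervention group will use electronic tools that nurses will check daily".
- **Intervention arm.** Forms are electronic. Section 2.4.2: "Research nurses will review the daily data from the IA patients to arrange appropriate reinforcement interventions (coaching".
- **Control arm.** Section 2.4.1: "They will fill out paper-form questionnaires collected by nurses during the monthly visits until the end of the study". It also says "Data collected by nurses during the monthly visits and by patients at home will be recorded in a specific database by the nurses", but that "these data will not be evaluated by nurses or oncologists during the study".
- **Other sources in Table 1.** There is a monthly CTCAE record by nurse or clinician and a separate patient-reported-outcome form at T0, T1, T2 and T3. Neither is limited to one arm.

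**The concern.** Daily review by nurses is a legitimate part of telenursing. The difficulty is that the record being reviewed is also listed as comparative data. In the intervention arm a missed day can be seen at the next daily check. In the control arm it can be seen at the earliest when the paper is handed in, and pages may be completed from memory just before the visit.

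These mechanisms can pull in different directions. Under-recording in the control arm would make telenursing appear to raise symptom incidence, or would hide a real benefit. Filling in from memory could inflate or reduce what control patients report. Randomisation does not protect against a measurement process that differs by arm. The tests in Section 2.7 cannot tell fewer events from fewer recorded events. The missing-data provision there cannot help with back-filled pages, because they do not look missing.

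At stake is a secondary comparison that Section 1.2 offers as evidence of effectiveness. The Section 1.2 objective of contrasting professional-reported events with patient reports is also affected if it draws on the daily record.

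**Working it through.** **1. Is the daily record comparative?** Section 2.4 says so directly. Section 2.6 links it to the adverse events in Section 1.2. The Section 1.2 sentence itself names CTCAE-based tools, which Table 1 schedules monthly by nurse or clinician. The daily record is therefore one stated source for the comparison, not clearly the only one.

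**2. Is capture equal?**

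| | Intervention | Control |
|---|---|---|
| Mode after baseline | electronic | paper |
| Reaches the nurses | daily | monthly visit |
| Reviewed during the study | daily | not evaluated |

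There is also a question of whether the control record exists. The daily-transmission sentence in Section 2.6 closes a paragraph that opens with the intervention group's electronic questionnaires, so it can be read as applying to that arm only. Section 2.4.1 mentions data recorded by control patients at home, which points the other way. On the first reading there is no control counterpart at all; on the second, capture is unequal.

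**3. How large could the effect be?** The plan gives no figure for diary completeness, so there is nothing to reproduce. All inputs below are assumptions.

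*Model A: gaps that last to the visit.* Visits are every 30 days. A gap starts on day g, uniform on 1 to 30, and runs to day 30. An event of d days starts on day s, uniform on 1 to 30. Recording resumes after the visit.

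- Mean days lost per gap: (1 + 2 + … + 30)/30 = 465/30 = 15.5.
- An event is wholly missed if g ≤ s and s + d − 1 ≤ 30. The number of such (g, s) pairs is 1 + 2 + … + (31 − d) = (31 − d)(32 − d)/2, out of 30 × 30 = 900.
- d = 3: 28 × 29/2 = 406; 406/900 = 45%.
- d = 5: 26 × 27/2 = 351; 351/900 = 39%.
- d = 7: 24 × 25/2 = 300; 300/900 = 33%.
- If an intervention-arm gap lasts one day, no event of 3 days or more is wholly missed.

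Share of control events lost = gap rate × the share above:

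| Patient-months with a gap | d = 3 | d = 5 | d = 7 |
|---|---|---|---|
| 10% | 4.5% | 3.9% | 3.3% |
| 20% | 9.0% | 7.8% | 6.7% |
| 30% | 13.5% | 11.7% | 10.0% |
| 50% | 22.6% | 19.5% | 16.7% |

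*Model B: capture probabilities.* Observed incidence = true incidence × capture probability. Take true incidence of 60% in control and 40% in intervention, a 20-point benefit.

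- Capture 95% intervention, 80% control: 0.60 × 0.80 − 0.40 × 0.95 = 0.48 − 0.38 = 10 points.
- Control capture 65%: 0.39 − 0.38 = 1 point.
- Control capture 50%: 0.30 − 0.38 = −8 points.
- Reversed (80% intervention, 95% control): 0.57 − 0.32 = 25 points.

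The same true effect can look halved, absent, reversed or enlarged.

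**The case against.** **The adverse-event comparison may not use the diary.** Section 1.2 names CTCAE-based tools, Section 2.4 says its adverse events are followed with them, and Table 1 makes them monthly. The Abstract and Section 3.1 place adverse events and patient-reported outcomes at one, three and six months, and Section 2.6 describes daily data as an addition. This stands in part. A reader might infer that the whole adverse-event comparison rests on the diary, and the documents do not support that. They do still declare the daily data comparative, so its role needs settling.

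**There are some completeness safeguards.** Section 2.4 has nurses advising patients in both groups to improve data collection. Section 2.5 allows exclusion after 15 days of missing data in either arm. Control forms pass through nurses' hands monthly, and not being evaluated need not mean not being checked for blanks. This stands for gaps found at the visit. It does not recover days already lost or detect back-filling, and the 15-day rule can be seen to apply much sooner in one arm than in the other.

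**The illustration is pessimistic.** Control patients may resume on their own, and the daily intervention checks are described as serving coaching, not the chasing of missed forms. Both points stand, so the figures are not estimates. A reader might also count every event as ending at day 30, which gives 465/900 = 52% whatever its duration. That overstates the loss, because an event still running after the visit can be recorded then.

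**Conclusion.** The concern holds for the daily patient record. As described, how fully and when it is captured depends on allocation, so a between-arm difference in it has no clear interpretation.

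The losses of about 3% to 23% of control events rest wholly on assumed gap rates of 10% to 50%, gaps lasting to the visit, and events of 3 to 7 days. They show that the problem could matter, not how large it is. A reader might infer a bias against telenursing, or one in its favour; the document supports neither, since direction depends on the balance of missed days and back-filling.

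The monthly CTCAE record and the T0 to T3 form are less exposed. They are not free of difficulty: Section 2.5 leaves patients and professionals unblinded, and Table 2 lists nurses for the monthly measurement in the intervention arm only. The primary outcome, supportive care needs at T1, is a scheduled questionnaire that does not use the daily record, and the sample size is untouched. This is a secondary-outcome issue worth correcting because the remedy is cheap.

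**What to change.** In Sections 1.2, 2.4, 2.6 and 2.7, state that:

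1. Between-arm comparison of symptoms and adverse events uses the T0 to T3 patient-reported-outcome form together with the monthly CTCAE record. The form should have the same items and recall period in both arms and, preferably, be completed in the same mode at the visit.
2. The daily record supports coaching in the intervention arm. It is reported descriptively by arm, with the proportion of days completed, and is not used for between-arm tests of incidence or severity.
3. The daily record is, or is not, kept in the control arm, so that Section 2.6 has one reading.

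The cost is mainly wording, since both instruments and the visits already exist. There are two downsides. Short events between visits will be caught only through the form's recall period, which the article does not state. Using one mode at the visit also slightly changes the intervention arm's electronic procedure at T1 to T3.
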